### Statistical methods

A detailed analysis plan will be defined and will be validated by the Scientific Council of the study. Subsequent modifications must be made before the database freeze and will be systematically approved by the Scientific Council.

The consistency of the data will be checked using logic checks and the database will undergo the necessary revisions before being declared frozen.

The statistical analysis will be conducted using SAS software version 9.4 (SAS Institute Inc., Cary, NC) or a later version. The significance threshold is set at 0.05 and all the tests will be performed with a two-sided test.

A descriptive analysis of the entire recruited population will be carried out to verify whether there are any deviations from the protocol at the time of inclusion. The quantitative variables will be expressed as mean ± standard deviation, medians and interquartile ranges. The qualitative variables will be expressed in numbers and percentages. At inclusion, the initial characteristics of the participants (socio-demographic characteristics, history of falls, ADL, EQ-5D-5L) will be described in both arms. The balance of randomisation will be checked by strata. The existence of a hospital centre effect will be explored.

### Primary outcome analysis

For the primary outcome, an intention to treat analysis will be conducted and will compare time to institutionalisation or death (before institutionalisation) between the two groups using a two-sided log-rank test in accordance with the sample size of the study. The subjects will be censored in case of an event occurrence or loss to follow-up. A sensitivity analysis will be conducted by a multi-variable survival model (with a Cox proportional-hazards model in the event that the risk proportionality hypothesis is verified) in order to take into account the stratification parameters and potential identified confounding factors (i.e. age and ADL). Marginal models with a robust variance–covariance matrix or sandwich estimator will be considered. Additional sensitivity analyses will be conducted taking into account the subjects who have been institutionalised (*i.e.* people placed in a nursing home) or who have already died at the time of their missed follow-up. The raw and adjusted hazard ratios will be expressed with their confidence interval set at 95%.

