Each CRA has a nominative account to connect to the ORU-Occitanie platform and can see patient forms with their identity (first name, last name,sex, age), contact details [phone number and identity of the caller (patient, family, other)], place of intervention, date and time of the incident, destination to which the patient was possibly referred to and name and phone number of participant’s GP whenever available and the reason for their calls. In order to check whether the daily ORU-Occitanie forms match the inclusion and non-inclusion criteria, the CRA is in charge of calling each subject and ensuring his/her eligibility to be enrolled in this study. Thereafter, the geriatrician investigator calls back the subject to give all the needed information about the study, obtains his/her oral informed consent and proceeds to his/her randomisation via the RISING-DOM electronic Case Report Form secured website (e-CRF). The actions/interventions planned for each group are detailed in Table 2. RISING-DOM is an open study. The enrolled participants, the investigators and the nurses are informed about the study group allocation after randomisation. However, the CRAs who are in charge of collecting data related to primary and secondary outcomes are not aware of this information in order to maximise data collection objectivity.

**Table 2 Tab2:** Details on planned actions/interventions in the RISING-DOM compared groups

***Intervention group***	***Control—usual care group***
CGA and fall record carried out at home by an experienced geriatric nurse at the first home visit	
PIP proposal discussed beforehand by a MDTM and with the GP to modify potentially reversible factors	
Commented delivery of PIP for the fall prevention and healthy aging and log-book providing throughout the nurse home visit	Standard recommendations of fall prevention and healthy aging and log-book sent by e-mail or a postal consignment
Nurse follow-up for implementing the PIP and ensuring its effective application or reporting the possible blocking points over the 24-month follow-up period (6 visits and 5 phone calls)	
CRA phone calls over the 24-month follow-up period to collect primary and secondary outcomes	CRA phone calls over the 24-month follow-up period to collect primary and secondary outcomes

*CGA* Comprehensive Geriatric Assessment [35], *PIP* Personalised Intervention care Plan, *MDTM* Multidisciplinary Team Meeting, *GP* General Practitioner, *CRA* Clinical Research Associate

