### Data collection procedure and randomisation

During the phone call, prior to the enrolment of each participant, the investigator collects information related to the patient’s medical history, his/her current list of pharmacological and non-pharmacological treatment, his/her lifestyle and previous history of falls.

After study recruitment and collection of baseline data, each participant is randomly allocated (1:1) to either the intervention or control arm. Blocked randomisation with random block sizes will be performed. The randomisation will be stratified according to lifestyle (living alone versus living with one’s relatives) and the existence or not of a history of a fall in the previous 12 months and the site.

Data on outcomes (death, hospitalisations, institutionalisation and number of additional EMS calls relating to falls) are collected prospectively by the CRA at 6, 12, 18 and 24 months (M6, M12, M18 and M24 respectively) of the patient’s follow-up and then every six months until the end of the study for both groups. The Activities of Daily Living (ADL) [34] and quality of life (EQ-5D-5L) [36, 37] scales are collected by the CRA once a year at inclusion, 12 and 24 months of follow-up. The exhaustive list of the variables collected by the CRA during the RISING-DOM study for all patients (intervention and control group) is summarised in Table 3. For both groups, a log-book is given to the participants to prospectively collect the events occurring during the follow-up period such as falls, hospitalisations and other side effects with their date. This aims to help the CRA collect with precision the occurrence of events. This document is not accessed/collected by the study team and it works simply as a memory aid. Data collected during nurse home visits (six visits) and nurse phone calls (five phone calls) for the “intervention group” are listed in Table 4.

**Table 3 Tab3:** RISING-DOM data and timeline collection and for ‘intervention group’ and ‘usual-care control group

	CRA call	Investing call	CRA calls					
		Enrolment allocation	Baseline assessment	Follow-up assessment				
	-t1	t0	M0	M6	M12	M18	M24	^b^
Screening for eligibility	+	+						

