**Unscheduled hospitalisation rate over 24 months**

**Time before occurrence of the first unscheduled hospitalisation**

**Death and institutionalisation rate over 24 months**

### Sample size

The 24-month event rate (institutionalisation or death before entering an institution) is estimated at 18% in the control arm based on available data in the literature [46]. A relative reduction of 30% is expected in the intervention arm at 24 months (Hazard Ratio = 0.679) with a two-sided test. 211 events should detect this Hazard Ratio (with a two-sided test Log-rank test) with a power of 80% and alpha risk of 0.05. With a study over 54 months, a uniform inclusion in the first 30 months and 10% of people lost to follow-up per year, it will be necessary to include 595 subjects per group to reach this number of events, thus 1,190 subjects in total.

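### The primary log-rank test leaves out age, which is known before randomisation; the test is valid and adequately sized, so this is a modest forgone gain in power and not a shortfall.

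*Protocol article*

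**What the plan says.** The Primary outcome analysis section fixes the deciding comparison. By intention to treat, the trial "will compare time to institutionalisation or death (before institutionalisation) between the two groups using a two-sided log-rank test". The reason given is that this matches the sample-size calculation. No covariate or stratum is attached to the test.

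Age appears one step lower, in a multivariable survival model labelled a sensitivity analysis, "in order to take into account the stratification parameters and potential identified confounding factors (i.e. age and ADL"). That model is to be fitted "with a Cox proportional-hazards model in the event that the risk proportionality hypothesis is verified". Raw and adjusted hazard ratios will both be reported with 95% confidence intervals.

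Three other places bear on the point:

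- **Timing.** Under Inclusion and exclusion criteria and recruitment procedure, the research associate who screens callers "can see patient forms with their identity (first name, last name,sex, age"), and Table 3 records date of birth in the pre-enrolment column. Allocation comes later: "After study recruitment and collection of baseline data, each participant is randomly allocated (1:1) to either the intervention or control arm".
- **Strata.** Randomisation is "stratified according to lifestyle (living alone versus living with one’s relatives) and the existence or not of a history of a fall". Fall history here covers the preceding year, and site is the third factor. Age is not among the factors.
- **Secondary outcomes analysis.** The percentage dead or institutionalised at 24 months is compared by a model adjusted for the stratification factors and for age. There, adjustment is the main analysis.

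**The concern.** In a randomised trial age does not confound the comparison in expectation. The reason to adjust for it is precision. If age predicts death or nursing-home entry in people of 70 and over, an unadjusted test compares arms across a mixture of high- and low-risk subjects. The estimated hazard ratio is then pulled towards 1 and the test loses some power. Adjusting for a value fixed before allocation recovers that power without raising the type I error.

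The plan adjusts for age when it analyses the two component events as a 24-month percentage, but not in the test on which the trial is decided. A log-rank test stratified by the randomisation factors would not supply the adjustment either, because age is not one of them. The Discussion section warns that recruitment was interrupted and that the target may be hard to reach, so efficiency that needs no extra subjects has some practical value here.

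**Working it through.** **1. The plan's own figures.** The control rate at 24 months "is estimated at 18% in the control arm based on available data in the literature", with a 30% relative reduction, so the intervention rate is 0.18 × 0.70 = 0.126. Under exponential times:

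- HR = ln(1 − 0.126) / ln(1 − 0.18) = 0.6786, against 0.679 stated.
- Schoenfeld events: 4 × (1.960 + 0.842)² / (ln 0.679)² = 210.
- Freedman events: [(1 + 0.679)/(1 − 0.679)]² × (1.960 + 0.842)² = 215.
- Power with 211 events: Φ(√211 × |ln 0.679|/2 − 1.960) = 80.3%.

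The 211 events and 80% power reproduce. The hazard ratio comes from overall, not age-specific, event rates, so 211 events already power the unadjusted test.

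**2. Expected events.** Take control hazard λ = −ln(0.82)/2 = 0.0992 per year, intervention hazard 0.679λ, loss hazard η = 0.10 to 0.105 per year, accrual A = 2.5 years and study length T = 4.5 years. The event probability in an arm with hazard λ is λ/(λ+η) × {1 − [e^(−(λ+η)(T−A)) − e^(−(λ+η)T)] / [(λ+η)A]}. This gives about 0.234 in control and 0.167 in intervention. Then 595 × (0.234 + 0.167) is about 239, or about 237 with the higher loss hazard. Both exceed 211.

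**3. Cost of leaving age out.** The article gives no standard deviation (SD) of age and no age effect, so both are assumptions. Trials of 1,190 subjects were simulated on the plan's inputs, with age as a standardised normal covariate. The unadjusted Cox test (equivalent to the log-rank) was compared with the age-adjusted one. Share of effective events lost = 1 − (mean z unadjusted / mean z adjusted)². With 4,000 trials per row (2,500 in the last):

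| Assumed age HR per SD | Mean z, raw | Mean z, adjusted | Loss | Power, raw | Power, adjusted |
|---|---|---|---|---|---|
| 1.40 | −2.888 | −2.931 | 2.9% | 83.0% | 84.4% |
| 1.49 | −2.869 | −2.930 | 4.1% | 82.3% | 83.7% |
| 1.65 | −2.863 | −2.953 | 6.0% | 83.0% | 84.7% |
| 1.82 | −2.739 | −2.870 | 8.9% | 78.2% | 81.8% |
| 1.95 | −2.741 | −2.919 | 11.8% | 78.0% | 82.9% |
| 2.23 | −2.630 | −2.890 | 17.2% | 74.6% | 82.4% |

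At 1.22 per SD the loss is about 1%; with no age effect it is nil. A loss of 3% to 11% therefore corresponds to about 1.4 to 1.9 per SD, or about 1.06 to 1.11 per year if the SD of age is 6 years. The gain in power over that range is about 1.5 to 5 points.

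The raw powers below 80% in the lower rows need care. The simulation sets 0.679 as the age-conditional hazard ratio, so the raw one drifts to about 0.69 to 0.70. The plan's 0.679 is the overall value, so these rows measure the difference between the tests, not a failure of the plan's target.

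**4. Cross-check from the plan's 211 events.** If the raw test has 211 effective events, the adjusted test behaves as if it had 211/0.97 = 217.5 to 211/0.89 = 237. The Schoenfeld formula gives 81.5% to 84.6%, against 80.3%: a gain of about 1.2 to 4.3 points.

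**5. Type I error.** In a separate run under the null (2,000 trials), rejection was 4.95% adjusted and 4.7% raw. The Monte Carlo standard error is √(0.05 × 0.95/2000) = 0.5 points, so both agree with 5%.

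**The case against.** The plan's choice is coherent. The test is valid and fully named, and it is the one the trial was sized for: "using a two-sided log-rank test in accordance with the sample size of the study". It needs no functional form for age and keeps its type I error without proportional hazards. The age-adjusted hazard ratio will be reported anyway, so the dispute is over which analysis is primary. All of this stands, and it is why the point is an improvement and not an error.

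Two parts carry less weight. The log-rank test is the score test of the unadjusted Cox model, so it too is most powerful under proportional hazards. Also, a robust variance, which the plan already contemplates, protects the adjusted test if proportionality fails, provided that its use does not hinge on a preliminary check.

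Stronger readings are tempting but unsupported:

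- **That the trial is underpowered.** Taking 3% to 11% off 211 events leaves about 205 to 188 and 79.1% to 75.6% power. But the 211 were derived for the unadjusted test from overall event rates, so nothing is to be subtracted from them.
- **That the plan calls age prognostic.** It calls age a potential confounding factor and states no effect on the outcome.
- **That 3% to 11% is a property of this trial.** It holds only under the assumed age effect.
- **That the efficiency is given up for nothing.** The unadjusted test buys simplicity and freedom from a model for age.

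**Conclusion.** The point holds as a modest efficiency improvement. The unadjusted log-rank test is valid and meets its stated power. An age-adjusted primary test would keep the type I error and add about 1.5 to 5 points of power if age has a hazard ratio of about 1.4 to 1.9 per SD, equivalent to recovering about 3% to 11% of effective events. Across 1.22 to 2.23 per SD the figure is about 1% to 17%. These sizes rest on an assumed age effect, a normal age distribution, exponential event times and proportional hazards; only the direction is firm. Any further gain from the randomisation factors was not estimated. The case is strengthened by the plan's own age adjustment in the main analysis of the 24-month percentage, for which the primary test has no counterpart.

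**What to change.** In Primary outcome analysis and in the detailed analysis plan, prespecify as primary the treatment test from a Cox model with age at enrolment as a continuous covariate. The model should also account for the randomisation factors (lifestyle, fall history and site), as the plan's existing adjusted model does. Use a robust variance and do not make the model conditional on a proportional-hazards pre-test. Keep the unadjusted log-rank test and raw hazard ratio as the sensitivity analysis. If the sponsor prefers the unadjusted test as primary, a sentence should say why this outcome alone goes unadjusted.

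ADL can stay in the sensitivity model. Table 3 first records the score in the column after allocation, although the text places baseline data collection before it, so it should not enter the primary model until that order is confirmed.

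The cost is a few words in the plan and no new data; the Statistical methods section allows changes before database freeze with the Scientific Council's approval. The downside is that the primary hazard ratio becomes conditional on age and strata, whereas the sample size used an overall one, and that the model relies on the chosen form for age, which should be fixed in advance.

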### Secondary outcomes analysis

The analysis of the secondary outcomes are conducted according to *(i)* a similar approach to that described for the analysis of the primary outcome for the criteria: time to the first additional EMS call relating to a fall and time to the first unscheduled hospitalisation *(ii)* the mean number of EMS calls relating to a fall, the mean number of unscheduled hospitalisations and the percentage of deceased or institutionalised subjects at 24 months will be compared between the two groups by generalised linear multi-variable models adjusted on the stratification and the potential confounding factors (age and AD, in particular) *(iii)* the comparison between the two groups of the level of the functional autonomy (ADL scale) and the quality of life ( EQ-5D-5L scale) at 24 months will be carried out by generalised multi-variable linear models adjusted to stratification and to the potential identified confounding factors (age) and the level of the score (ADL or EQ-5D-5L at inclusion) if appropriate.

Additional per protocol analysis will be conducted in the population of subjects who have complied with the protocol (in the intervention arm having accepted at least 80% of all visits and calls proposed during follow-up and for whom a PIP will have been proposed).

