**Time before occurrence of the first additional EMS call relating to a fall**
This represents the time between the first fall recorded at enrolment time (t0) and the occurrence of the first additional EMS call relating to a fall over 24 months.

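### The 24-month percentage dead or institutionalised is compared by GLM although the plan expects 17–18% of each arm to be lost by then; the count estimand and one time zero also need reconciling (minor)

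*Protocol article*

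**What the plan says.** **Percentage and counts.** Under Secondary outcomes analysis, item (ii), the mean number of fall-related EMS calls is listed first, and then "the mean number of unscheduled hospitalisations and the percentage of deceased or institutionalised subjects at 24 months will be compared" between groups by generalised linear multivariable models. These are adjusted for the stratification factors and potential confounders.

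**Outcome definitions.** In the Secondary outcomes list, EMS calls and unscheduled hospitalisations are each labelled a *rate* over 24 months. The analysis section compares a *mean number*.

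**Loss.** The Sample size section assumes "10% of people lost to follow-up per year". The Primary outcome analysis section states censoring at loss, and sensitivity analyses for people found to be institutionalised or dead at a missed follow-up. The text on the 24-month percentage and counts mentions neither.

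**Time to first event.** First EMS call and first unscheduled hospitalisation follow "a similar approach to that described for the analysis of the primary outcome for the criteria". For the first call the definition reads "This represents the time between the first fall recorded at enrolment time (t0" and ends at the next call. The Primary outcome section counts days from enrolment (t0), and Table 3 places allocation at t0.

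**Follow-up.** Under Outcomes, the last participant enrolled has 24 months of follow-up and the first has 54. Everyone is therefore planned to have the full 24-month window.

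**The concern.** A percentage at a fixed time can be read from a binary GLM only if each person's status at that time is known. Here the plan itself expects more than one person in six to be lost before month 24 without an event. A binary GLM with no weighting, imputation or pseudo-values must either count them as event-free or drop them. Both give absolute risks that disagree with the Kaplan-Meier curve of the primary analysis, on the same event in the same people.

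Unequal loss would also move the contrast between arms, and the design makes it plausible. Only the intervention arm has six nurse visits and five nurse calls, and Table 4 has the nurse check contact details at ten of those eleven contacts. The documents give no figure for differential loss.

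For counts, a rate and a mean number are different quantities once people die or are lost. The definition names one and the analysis names the other. For the first call, a clock that starts at the fall includes the days between the fall and randomisation. A clock that starts at enrolment does not.

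**Working it through.** **Inputs (Sample size section).** "The 24-month event rate (institutionalisation or death before entering an institution) is estimated at 18% in the control arm"; 30% relative reduction, so 0.70 × 18% = 12.6% in the intervention arm; loss 10% per year; 1:1 allocation. Constant hazards are assumed.

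**The plan's own figures first.** HR = ln(1 − 0.126)/ln(1 − 0.18) = 0.679, as stated. Schoenfeld events = 4(1.960 + 0.842)²/(ln 0.679)² = 209.5, so 210. Freedman's formula gives 215. The stated 211 lies between them, and 211 events give 80.3% power. The inputs are coherent.

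**Monthly hazards.**
- Event, control: λ₀ = −ln(0.82)/24 = 0.00827
- Event, intervention: λ₁ = −ln(0.874)/24 = 0.00561
- Loss: η = −ln(0.90)/12 = 0.00878

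**Status at month 24.** Event seen = λ/(λ+η) × [1 − e^(−24(λ+η))]. Event-free and still followed = e^(−24(λ+η)), that is 0.82 × 0.81 and 0.874 × 0.81. The remainder is lost before any event.

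| | Control | Intervention | Ratio |
|---|---|---|---|
| Event seen by 24 months | 16.3% | 11.4% | |
| Followed, event-free | 66.4% | 70.8% | |
| Lost before any event | 17.3% | 17.8% | |
| Planned risk | 18.0% | 12.6% | 0.700 |
| Lost counted as event-free | 16.3% | 11.4% | 0.699 |
| Lost dropped: seen/(seen + followed) | 19.7% | 13.9% | 0.704 |

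**Unequal loss (assumption: 5% per year in one arm, 10% in the other).**

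| Loss per year, control / intervention | Ratio, lost as event-free | Ratio, lost dropped |
|---|---|---|
| 10% / 5% | 0.736 | 0.670 |
| 5% / 10% | 0.665 | 0.737 |

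**Counts, no true effect on the rate.** The ratio of mean counts equals the ratio of mean time at risk in the window.
- If every composite event ended counting, mean time is 0.18/0.00827 = 21.77 months v 0.126/0.00561 = 22.45 months, ratio 1.03.
- If only deaths end counting, and deaths are 25% to 75% of composite events (assumption), the ratio is 1.01 to 1.02.
- With a shared log-normal frailty of SD 0.7 to 1.0 (assumption) it is 1.05 to 1.08. An offset lowers this to 1.02 to 1.04 but does not remove it.
- Unequal loss matters for hospitalisations, which are collected by telephone. With all composite events ending counting, observed time is 19.70 v 21.37 months (loss 10% / 5%), ratio 1.08, or 20.72 v 20.29 months (5% / 10%), ratio 0.98.

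**Time zero.** The listing of EMS calls comes first, then the CRA's eligibility call, then the investigator's call with consent and randomisation. The fall therefore precedes randomisation. The first-call definition attaches t0 to the fall, while the Primary outcome section and Table 3 attach it to enrolment. The length of the gap is not stated, so no bias can be computed.

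**The case against.** The strongest reply is that much of this is silence. A GLM can carry a log-time offset, and it can be combined with weighting, multiple imputation or pseudo-values. A detailed analysis plan is announced, and such details are commonly left to it. This stands: the article does not say that the models are unweighted or without an offset. What remains is that the article itself names the endpoint (a percentage at 24 months) and the model class while planning for 17–18% unknown status, and that two of its definitions conflict.

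Stronger readings are tempting, and the documents do not support them:

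- *The percentage ignores death.* It does not, because death is part of the composite. Only loss is at issue, and with equal loss the ratio moves by less than 0.005.
- *A beneficial intervention could look neutral or harmful on calls and admissions.* The drift from longer survival is about 1–3% on the plan's rates, too small for that.
- *Loss shortens the capture of EMS calls.* These come from the regional observatory platform and are only verified by telephone, so losing phone contact need not end their capture. For other outcomes, relatives and the GP are fallback sources.
- *Staggered entry makes time at risk unequal.* Everyone is planned to have 24 months.
- *Censoring first events at death is invalid.* It gives a valid cause-specific comparison, and the article promises hazard ratios. It does not say that it will report one minus Kaplan-Meier as an absolute risk.

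The mean number per randomised person is also a legitimate quantity. The Background gives lower resource use for fall-related calls as a reason for the project, and total burden answers that directly. The loose time zero is not shown to bias the comparison, since time before randomisation is balanced by randomisation.

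**Conclusion.** The point holds as a minor one, in three parts.

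1. The 24-month percentage is poorly served by an ordinary GLM. Absolute risks would be about 1 to 2 points away from the planned 18.0% v 12.6%. The ratio is safe if loss is equal and runs from about 0.66 to 0.74, against 0.70, if loss is 5% v 10% per year. This rests on constant hazards and loss independent of outcome. The unequal-loss figures are an assumption.
2. *Rate* and *mean number* must be reconciled for calls and hospitalisations. The inflation of raw counts against the intervention is about 1–3% without frailty. Unequal loss could add more for hospitalisations, in either direction.
3. The first-call clock and the primary clock start at different points as worded. The size of this cannot be computed from the article.

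A reader might infer that the secondary results are biased by the very effect that the trial hopes to show. Under the plan's own figures that effect hardly moves them. Differential loss is the real exposure, and the documents neither state it nor rule it out.

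**What to change.** - **Percentage dead or institutionalised:** estimate it at 24 months as the Kaplan-Meier difference between arms with its confidence interval. Where adjustment is wanted, use a GLM on pseudo-values. It then agrees with the primary curve.
- **EMS calls and unscheduled hospitalisations:** name one estimand. Use a rate from a negative binomial model with log observed time, up to 24 months, as offset. Report the mean number per randomised person beside it. For calls, define observed time by the platform's coverage and not by phone contact.
- **Time zero:** use randomisation for all time-to-event outcomes and reword the first-call definition to match.
- **Optional:** cumulative incidence of first call and first admission with death as a competing event, beside the cause-specific hazard ratio.

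The cost is a few sentences and a little more programming, and no data beyond the event and last-contact dates that the primary analysis already needs. The article allows analysis-plan changes before database freeze. There is one trade-off: a rate while alive answers a slightly different question from total burden, which is why both should be shown. The offset reduces bias from differing survival or loss, but does not remove it when frail people both fall more and die sooner.

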***Sociodemographic & medical data***								
Date of birth	+							
Sex	+							
Participant personal data	+							
GP information data	+							
Date, hour and location of fall	+							
Fall circumstances and consequences	+							
Legal protection measures	+							
Education level	+		+					
Life style (living alone or with a partner, family, etc.)		+						
Domestic aid			+					
Medical history		+						
Fall history in the last 12 months		+						
Medical and non-medical treatments		+						
Number of hospitalisations in the last 6 months			+					

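### The baseline hospitalisation count, collected in both arms, is not among the covariates named for the unscheduled-hospitalisation models; naming it would be a small efficiency gain of unknown size

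*Protocol article*

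**What the plan says.** Under Data collection procedure and randomisation, the article states that the list of variables collected by the clinical research associate "for all patients (intervention and control group) is summarised in Table 3". One baseline item there is "Number of hospitalisations in the last 6 months", marked in the M0 column, the same column as the baseline ADL and EQ-5D-5L.

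Under Secondary outcomes analysis, three kinds of model are described:

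- Item (i), time to first unscheduled hospitalisation, follows "a similar approach to that described for the analysis of the primary outcome". That means a two-sided log-rank test, then a multivariable survival model as a sensitivity analysis, meant to "take into account the stratification parameters and potential identified confounding factors (i.e. age and ADL").
- Item (ii), the mean number of unscheduled hospitalisations, uses "generalised linear multi-variable models adjusted on the stratification and the potential confounding factors (age and AD, in particular").
- Item (iii), ADL and EQ-5D-5L at 24 months, adjusts for stratification, age and "the level of the score (ADL or EQ-5D-5L at inclusion) if appropriate".

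Randomisation is "stratified according to lifestyle (living alone versus living with one’s relatives) and the existence or not of a history of a fall"; site is the third factor, and the fall history covers one year. None of these factors measures earlier hospital use.

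**The concern.** A participant's recent hospital use is the closest baseline measure of the outcome in items (i) and (ii). The plan uses the baseline value where the outcome is a scale, but names none where the outcome is hospitalisation, although the form collects one.

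If earlier admissions predict later ones, two things follow. In the count model, between-person variation that has already been measured stays in the residual, and the interval for the treatment effect is wider than it need be. In the survival analysis, the adjusted model gives up some power for the conditional hazard ratio. This matters a little more than usual because the Discussion warns that the planned sample size may not be reached.

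**Working it through.** **The plan's own figures.** The article gives no rate, variance, correlation or power for unscheduled hospitalisations, so there is no figure on this point to reproduce. The only sizing figure is the 211 events for the primary outcome. At a hazard ratio of 0.679 with 80% power and two-sided 0.05, Schoenfeld's formula gives 4 × (1.960 + 0.842)² / (ln 0.679)² = 210, and Freedman's gives 215. That figure is sound but says nothing about hospitalisations.

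**Count model, against no adjustment.** Let ρ be the correlation between the baseline count and the follow-up count (assumed). Adjustment multiplies the variance by 1 − ρ² and the standard error by √(1 − ρ²). A comparison with 80% power before adjustment then has power Φ((1.960 + 0.842)/√(1 − ρ²) − 1.960).

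| ρ (assumed) | Variance × | Standard error × | Power, from 80% |
|---|---|---|---|
| 0 | 1.00 | 1.000 | 80.0% |
| 0.1 | 0.99 | 0.995 | 80.4% |
| 0.2 | 0.96 | 0.980 | 81.6% |
| 0.3 | 0.91 | 0.954 | 83.6% |
| 0.4 | 0.84 | 0.917 | 86.4% |
| 0.5 | 0.75 | 0.866 | 89.9% |

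A simulation of Poisson models with robust standard errors agrees. It used 1,190 subjects, gamma frailty, a rate ratio of 0.8 and 300 runs per scenario. The ratio of adjusted to unadjusted standard error was 1.00 at ρ = 0, 0.985 at 0.17, 0.94 at 0.35, 0.91 at 0.41 and 0.86 at 0.50.

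**Count model, beyond the planned adjustment.** The table overstates the benefit, because item (ii) already adjusts for the strata, age and, reading AD as ADL, for ADL. As an illustration, assume that ADL and the outcome, the count and the outcome, and ADL and the count all correlate at 0.3 in absolute value, with signs such that ADL and the count carry overlapping information:

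- Residual variance with ADL alone: 1 − 0.09 = 0.91.
- R² with both: (0.09 + 0.09 − 2 × 0.3 × 0.3 × 0.3)/(1 − 0.09) = 0.126/0.91 = 0.138, so the residual variance is 0.862.
- Ratio: 0.862/0.91 = 0.947. The added variance reduction is about 5%, not 9%, and the standard error falls by about 3%.
- Power from 80%: Φ(2.802/√0.947 − 1.960) ≈ 82%, not 84%.

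**Time to first unscheduled hospitalisation.** The log-rank test is unchanged whatever covariates are named, so only the adjusted model is affected. A Cox simulation used 1,190 subjects, the plan's accrual and 10% yearly loss. It assumed a treatment hazard ratio of 0.8, 30% of participants with a prior admission, and 40% or 60% admitted by 24 months. Power without and with the covariate was:

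| Hazard ratio for prior admission (assumed) | 40% admitted | 60% admitted |
|---|---|---|
| 1.5 | 0.72, 0.72 | 0.84, 0.86 |
| 2 | 0.70, 0.72 | 0.82, 0.86 |
| 3 | 0.63, 0.71 | 0.73, 0.84 |

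A rerun with these settings gave gains of similar size. The standard error of the log hazard ratio was practically the same with and without the covariate: the power comes from a conditional hazard ratio further from 1, not from a narrower interval. These figures too are against an unadjusted model.

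**The case against.** The strongest reply is that this is detail for the analysis plan, which the article announces and which is not shown. The words in particular in item (ii) make age and ADL examples. A reader might infer that the plan excludes hospital history; the text does not support that. The primary-outcome section introduces its list with i.e., which reads as closed, but item (i) adopts only a similar approach. This stands, and it limits the point to a recommendation.

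A reader might also infer bias, or take a raw hazard ratio nearer to 1 as an error. Neither follows. Leaving a prognostic covariate out of a randomised comparison does not bias it. The raw and adjusted hazard ratios are marginal and conditional quantities, and the article reports both.

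Nor is the different treatment of ADL and EQ-5D-5L a contradiction. There the same scale is measured twice. Here an all-cause 6-month count would stand in for unscheduled admissions over 24 months. It also rests on recall, in a population where about 58% of the pilot sample had an MMSE of 24 or below. All of this lowers the likely correlation.

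The timing objection is weaker. Table 3 places the item at the M0 call, after allocation at t0, while the text puts baseline data before allocation, and participants know their arm. But the caller is blind to the arm, and the baseline ADL and EQ-5D-5L, which the plan already uses, sit in the same column. What remains is that Table 3 lists a number and not dates, so the look-back has to be fixed by how the question is asked.

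**Conclusion.** The point holds as a small efficiency improvement. The count is collected in both arms, no stated hospitalisation model names it, and item (iii) shows that the plan accepts baseline adjustment elsewhere.

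The documents do not give the size. For the count comparison, it is a standard error about 0.5% to 13% smaller than without adjustment if the correlation lies between 0.1 and 0.5, less beyond the planned covariates, and nothing at zero correlation. For time to first hospitalisation, the lead test does not change. The adjusted model might gain 0 to 2 points of power if prior admission has a hazard ratio of 1.5, and 8 to 11 points only if it is 3, both against an unadjusted model. A reader might conclude that precision is certainly being lost; without a correlation, the documents cannot show that.

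**What to change.** - In item (ii) of Secondary outcomes analysis, name the baseline hospitalisation count, for example as 0, 1, or 2 or more, as a prespecified covariate in the model for the number of unscheduled hospitalisations.
- In item (i), add it to the adjusted survival model for time to first unscheduled hospitalisation, reported beside the log-rank test.
- Define the look-back as the 6 months before enrolment (t0), and say whether the index stay of under 24 hours counts.
- State how missing M0 answers are handled.
- Correct AD to ADL in the same sentence.

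This takes a sentence or two in the analysis plan. The article allows changes before database freeze with the Scientific Council's approval. No extra visits or participants are needed. The costs are one more model term (two coefficients with the grouping above) and a simple rule for missing values. For participants already called, the look-back can be checked only if admission dates were recorded, which Table 3 does not show.
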